## **2.8 Study treatments**

### **2.8.1 Treatment Groups**

There will be two treatment groups namely GROUPS A and B. One treatment group will be of participants receiving ART and 75mg of ASA (GROUP A) and the other group will be of participants receiving ART and placebo (GROUP B).

#### **2.8.1.1 Description of study drugs**

All the study drugs (ASA and placebo) will be manufactured by *Cosmos Limited* in tablet form and will be packaged in blister packs in boxes. The placebo will have a similar color, shape, taste and size to the active drug. The boxes containing the study drugs will have the following information; batch number, expiry date and the statement “keep all medicines out of the reach of children”. Also, arbitrary study letter and month number will be hand written on the boxes.

#### **2.8.1.2 Dosage and Route of Administration**

Participants will self-administer one tablet of either 75mg ASA or placebo in addition to their ARV drugs. This will be taken daily at evening times together with their ARV drugs and swallowed whole with plenty of liquid (e.g. a glass of water) preferably after a meal. This should be continued for the six months of treatment and follow- up.

#### **2.8.1.3 Dose modification**

There will be no any allowable dose modifications.

### **2.8.2 Dispensing and Study Drug Accountability**

The study drugs will be stored in a pharmacy for each study site in an identified lockable wooden cabinet where temperature will be controlled between 25° Celsius and 30° Celsius. A temperature log will be maintained. Study drug dispensing will be done by a respective pharmacist (CTC staff employed in the study) who will be provided with the randomization schedule. The pharmacist at each site will maintain accurate records of the receipt of all study medication, including dates of

receipt. In addition, accurate records will be kept regarding when and how much study medication is dispensed and used by each patient in the study. At the end of the study, there will be final reconciliation of study drug received, dispensed and consumed. Any discrepancies will be investigated, resolved and documented by the study team. Unused study drug will be destroyed at the end of the study.

### **2.8.3 Measurement of subject compliance**

Unlike with ARV drugs where there are cut- off points to define good or low adherence depending on method used to measure adherence, with ASA there are no. Hence in the proposed study, compliance to study drugs will be defined as adherence to ASA therapy for at least 22 days in a month and will be assessed monthly. This is adopted from a study that was looking at frequency and predictors of non-compliance to ASA therapy in post MI patients where noncompliance was defined as non-adherence to ASA therapy for more than 2 days per week(57). When translated to a month ( 30 days), then adherence to ASA therapy for at least 22 days in 30 days is compliance. Assessment of compliance to study drugs will be by pill count. At each visit, patients will be given their study drug refill and will be asked to return with the study drug boxes in the subsequent visit. Patients will be provided with study drug pills to suffice 30 days to take home. To measure compliance, extra tablets to the 30 tablets will be provided at each monthly visit. The number of the extra tablets will be changing so that the number of tablets remaining in each month will not be fixed. This will keep the patients from predicting the number of tablets to remain in the study drug box. Patients' remaining monthly tablets of their study drugs will be counted, by the study doctor, to ascertain compliance at each monthly follow up visit. Overall compliance will be the average of the monthly compliances. Subject's compliance will be recorded on the case report forms (CRFs)

### **2.8.4 Excluded medications and treatments**

In addition to the study drugs, during the study the participants will be continuing with the HIV/AIDS standard treatments i.e. ARV drugs and prophylaxes against opportunistic infections. After being recruited into the study if it becomes clinically essential that the participant must take antiplatelets, anticoagulants and/or methotrexate then the patient will be withdrawn from the study. Over the counter ASA will not also be permitted during the period.

NSAIDs will have to be avoided wherever possible but short term intermittent NSAID use will be allowed. NSAIDs should not be co-administered with the trial treatment for more than 2 consecutive weeks. Paracetamol can be considered as an alternative analgesic and will be permitted within the study. The use of co- medications will be checked at each visit and will too be recorded on the CRFs.

## **2.9 Subject enrolment and randomization**

### **2.9.1 Recruitment**

Subjects will be recruited from CTCs in Dar es Salaam. Patients attending CTCs at each site will be informed about the proposed study at the CTCs and will be invited to participate by the study nurses and doctors (who are also CTC staff). Prior to performing any study specific procedure (including screening procedures to determine eligibility), a signed consent form will be obtained for each subject once they have been diagnosed to be HIV- infected. The consent form will describe the purpose of the study, the procedures to be followed, and the risks and benefits of participation. The study nurse who will be part of the CTC staff and well informed of the study protocol, will conduct the informed consent discussion and will check that the subject comprehends the information provided and answer any questions about the study. Should there be an issue raised by the patients that the study nurse cannot address, the study doctor will be at hand to assist. Consent will be voluntary and free from coercion. The study nurse that will have conducted the consent discussion will also sign the informed consent form. A copy of the consent form will be given to the subject and the fact that the subject has been consented to the study will be documented in the subject's record. Then, a screening number will be given to the already consented patient by the study nurse. The patient will be attended by the study doctor and assessed for eligibility. When all the inclusion and exclusion criteria have been addressed and the eligibility of the subject confirmed, the subject will be consecutively recruited into the study and will be given a study number by the study doctor. The patient will go with the study number to the pharmacy and show it to the study pharmacist. The study pharmacist will give a box containing the study drugs according to the study number and the randomization schedule.

On average, 10 patients will be registered for care per week at each study site making 20 patients per week and 80 patients per month. Therefore, for 454 patients the recruitment is expected to last

for at least 6 months. Reasons for ineligibility for patients and reasons for non-participation of eligible subjects will be documented.

### **2.9.2 Eligibility Criteria**

Patients will be assigned to a randomized study treatment only if they meet all of the inclusion criteria and none of the exclusion criteria.

#### **2.9.2.1 Inclusion Criteria**

Each patient must meet all of the following criteria to be enrolled in this study:

- Consenting newly recruited male or female HIV-infected patients
- ARV drugs naïve initiating on ARV drugs
- Aged 18 years and above
- Willing to stay in Dar es salaam for at six months
- Willing to attend HIV clinics at **Mwananyamala** or Mbagala Rangi Tatu hospitals for at least six months

#### **2.9.2.2 Exclusion Criteria**

Patients meeting any of the following criteria will be excluded from the study:

- Previous intolerance or allergy to ASA or any ASA products
- Asthmatics
- Predisposition to bleeding
- Antithrombotic therapy
- Therapy with prohibited drugs (see appendix 5)
- Active or history of peptic ulcer disease
- Pregnancy
- Severe renal disease (eGFR <30 ml/min/1.73 m^2)

### **2.9.3 Randomization Procedures**

Randomization will be performed separately at each study site. Each study site will have 227 eligible participants. Patients will be randomly assigned to receive either 75mg ASA or a placebo in a ratio of 1:1. A statistician who will not be part of the study will prepare the randomization

schedule using block randomization of 23 blocks. The randomization schedule will contain study numbers against their respective arbitrary study letters (P and Q) representing the study treatment groups A and B. The statistician will be aware of which arbitrary study letter represents which study treatment group and hence study drug. The randomization schedule will be sent to an independent pharmacist for labeling (handwriting arbitrary study letter and month number) of the study drug boxes. The bottles containing the study drugs and the randomization schedule will then be sent to the pharmacy at the respective study sites. The schedule will be provided to the study pharmacist (recruited from CTC staff) and sealed envelopes containing the treatment allocation of each randomization code will remain with the statistician who will give it to the investigator at the time of data analysis.

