#### **2.9.4 Blinding Arrangements**

This will be a double- blinded study where all members of the research team and the subjects will be blinded to treatment allocation. Only the statistician who will make the randomization schedule and the independent pharmacist who will label the study drug boxes with the arbitrary study letters will be unblinded.

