#### **2.9.5 Breaking of the Study Blind**

##### **2.9.5.1 On Study**

Breaking the code will only occur upon recommendation by the Data and safety monitoring board (DSMB) during the study duration i.e. before completion of the study.

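### Two arm-level letters on every box, with the letter list held at the site pharmacy, mean that decoding one letter reveals all 454 allocations

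*Protocol*

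**What the plan says.** Protocol section 2.9.3 sets out the code: "The randomization schedule will contain study numbers against their respective arbitrary study letters (P and Q) representing the study treatment groups A and B". There is one letter per arm. Section 2.8.1.1 states that the "arbitrary study letter and month number will be hand written on the boxes". The other label items it lists are batch number, expiry date and a child-safety statement. No participant or kit number is described.

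Section 2.8.3 has patients take the boxes home, and they "will be asked to return with the study drug boxes in the subsequent visit". At each monthly visit the "remaining monthly tablets of their study drugs will be counted, by the study doctor". Under section 2.9.1 the study doctor also confirms eligibility and issues the study number to consecutive recruits.

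Section 2.8.2 gives dispensing to the "respective pharmacist (CTC staff employed in the study) who will be provided with the randomization schedule". Section 2.9.1 has this pharmacist look up the study number on that schedule and hand over the box.

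Section 2.9.4 states that "all members of the research team and the subjects will be blinded to treatment allocation", and names only the schedule statistician and the independent labelling pharmacist as unblinded. Section 2.9.3 leaves sealed envelopes with the statistician. Section 2.9.5.1 allows a code break during the study only on the recommendation of the data and safety monitoring board.

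**The concern.** A two-letter code is a single secret shared by the whole trial. Before anyone knows what P and Q mean, the label already sorts patients into the two arms, in view of patients, study doctors and site pharmacists. Side effects can then be tallied by letter. The protocol itself supplies the clues: section 1.1 names gastrointestinal bleeding as an aspirin risk, section 2.11.2 has epigastric pain and black stools asked about at follow-up, and section 2.15.1 stops study drug if bleeding occurs. Matched tablets do not hide any of this.

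Once a letter is decoded the loss is total and cannot be repaired. Every past allocation can be read from the boxes, and every future one from the pharmacist's list. The judgements most open to influence are the relatedness of adverse events (section 2.12.2), morbidity reported by patients at visits (section 2.11.7), monthly adherence counselling (section 2.10) and investigator-led withdrawal from study treatment (section 2.9.6.1).

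**Working it through.** **1. How many allocations one decoded letter reveals.** Inputs: 454 participants, 227 per arm (section 2.13.1); 2 codes (section 2.9.3); 227 per site (section 2.9.3).

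- As written: knowing P gives Q, so 454 of 454 are revealed.
- If the letters were assigned separately at each site (not stated): 227 of 454.
- With a unique code per participant: 1 of 454, or 1/454 = 0.2%.

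**2. Who can see what, from the text alone.**

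| Person | Sees the letter on boxes | Sees letters of future study numbers | Meant to know the arm |
|---|---|---|---|
| Patient | yes (own boxes) | no | no |
| Study doctor | yes (returned boxes) | not given the list | no |
| Site pharmacist | yes | yes | no |
| Schedule statistician, labelling pharmacist | yes | yes | yes |

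The first three are formally blind because the letters are arbitrary. Nothing described hides the grouping from them.

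**3. How likely a tally by letter points the right way.** The protocol gives no side-effect rates by arm, so these are assumptions: six-month rates of 10% v 5%, or 7% v 5%, for aspirin v placebo. Further inputs:

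- 227/2 ≈ 113 patients per letter per site.
- Recruitment is uniform over six months (section 2.5 gives a six-month recruitment period).
- Events are spread evenly over each patient's six months.

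Share of each patient's events seen so far:

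- Month 3 of recruitment: about 57 per letter, mean follow-up 1.5 of 6 months = 25%.
- End of recruitment: 113 per letter, mean follow-up 3 of 6 months = 50%.
- After all follow-up: 113 per letter, 100%.

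The observer picks the letter with more events. With independent binomial counts X (aspirin letter) and Y (placebo letter), P(correct) = P(X > Y) + ½ P(X = Y).

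| Time | n per letter | Rates so far (10% v 5%) | P(correct) | Rates so far (7% v 5%) | P(correct) |
|---|---|---|---|---|---|
| Mid-recruitment | 57 | 2.5% v 1.25% | 0.68 | 1.75% v 1.25% | 0.58 |
| End of recruitment | 113 | 5% v 2.5% | 0.84 | 3.5% v 2.5% | 0.67 |
| After all follow-up | 113 | 10% v 5% | 0.92 | 7% v 5% | 0.74 |

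Normal check on the last row, with mean difference n(p₁ − p₂) and SD √[n(p₁(1 − p₁) + p₂(1 − p₂))]:

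- 10% v 5%: Φ(5.65/3.94) = 0.92.
- 7% v 5%: Φ(2.26/3.57) = 0.74.

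Pure guessing is 0.50. These are chances of decoding a letter at one site. They do not measure bias in any outcome, which the document does not allow to be quantified.

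**The case against.** The letters are arbitrary, the tablets are matched, the envelopes stay with the statistician, and a break needs a board recommendation. A blind guess is right half the time, and a formal break harms the trial only if its result reaches people who see the boxes. All of this stands. It lowers the chance that a letter is decoded but does not limit the damage afterwards.

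Four stronger readings are tempting and are not supported.

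- *Concealment is already lost.* Section 2.9.1 has eligibility confirmed and the study number issued before the patient reaches the pharmacy, and the schedule goes to the pharmacist. The enrolling doctor can foresee assignments only if a letter has been decoded and the pharmacist's upcoming letters are also shared.
- *A doctor would be right 92% of the time during the trial.* That figure needs complete follow-up of every patient, when no allocation is left to foresee and nearly all judgements are made. While recruitment runs, the same assumptions give 68% rising to 84%, or 58% rising to 67%.
- *Expedited safety reports will force trial-wide unblinding.* Section 2.12.4.2 sets reporting times and says nothing about opening the code.
- *The block count shows that the list is defective for blinding.* Section 2.9.3 gives 23 blocks for 227 patients per site. An odd 227 cannot split exactly 1:1 under any scheme, and the count says nothing about who can read the code.

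It is also fair to say that the envelopes may already be one per study number, since section 2.9.3 speaks of the allocation of each randomization code. With shared letters that gives little individual protection: whoever learns one result and sees the boxes can read the rest.

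**Conclusion.** The labelling scheme is a real weakness, and it is stated in the protocol rather than left open. Two visible arm-level letters let site staff group patients by treatment. One decoded letter, or one code break that becomes known at the sites, reveals 454 allocations instead of 1. Under the assumed rates, decoding from side effects is only modestly better than chance midway through recruitment (68% or 58%) and becomes likelier later (84% or 67% at the end of recruitment; 92% or 74% after all follow-up).

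A reader might infer that the primary result is compromised. The documents do not show that. Viral load is measured by assay (section 2.11.6), and specimens leaving the site carry only the study number (section 2.15.1). The primary outcome is exposed only indirectly, for example through counselling or withdrawal decisions. The direct threat is to adverse-event attribution, self-reported morbidity, counselling and withdrawal decisions. The case for changing the scheme rests on the size of the loss if it happens, and on how little prevention costs before the first enrolment.

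**What to change.** Before enrolment, change sections 2.8.1.1, 2.8.2 and 2.9.3 as follows:

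- The independent pharmacist labels and pre-packs the boxes by unique study number and month, with no group letter.
- Each site pharmacy receives a list of study numbers without letters. The list linking number to arm stays with the statistician and the independent pharmacist.
- The text states that the sealed envelopes are one per participant, so that one code can be opened without revealing any other.

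The batch number is also on the boxes, and the protocol does not say whether it differs between aspirin and placebo. If it does, it would sort patients as the letter does, so this should be checked when the labels are redrawn.

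Cost: different handwriting on about 454 × 6 = 2,724 boxes (taking one box per participant per month) and a reissued list. The labels are already to be written by hand, so only their content changes. The downside is that boxes can no longer be swapped between patients, which calls for slightly more stock planning.

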#### **2.9.4 Blinding Arrangements**

This will be a double- blinded study where all members of the research team and the subjects will be blinded to treatment allocation. Only the statistician who will make the randomization schedule and the independent pharmacist who will label the study drug boxes with the arbitrary study letters will be unblinded.

#### **2.9.5 Breaking of the Study Blind**

##### **2.9.5.1 On Study**

Breaking the code will only occur upon recommendation by the Data and safety monitoring board (DSMB) during the study duration i.e. before completion of the study.

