### 2.5 Expected duration of study population

The proposed study is expected to run for 1 year, from start of subject screening to last subject finishing the study. The recruitment period will be six months and each individual

subject will be on study treatment for six months and will also be followed- up for six months.

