##### **2.9.5.2 Following Completion of the Study**

The study drug codes will only be available once all data collected will have been entered into the database for every participant and the data base has been finalised.

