The investigator and statistician will be responsible for data analysis. Staff will also be responsible for coordinating the response to any SAE's that arise during the course of the trial and reporting these if indicated to the investigator, who will then report to the appropriate board/committee. Continuous study monitoring will be performed by the investigator in collaboration with an internal monitor who will closely follow up and review study progress, adverse events, any protocol deviations, laboratory data and clinical information. The data and safety monitoring board (DSMB) will also independently monitor the study at intervals to review progress reports, safety data, trial performance and progress and make pertinent recommendations to research ethics committees, regulatory authority, directorate of research and publications at MUHAS and the investigator. The DSMB will comprise of a clinical pharmacologist, a physician and a biostatistician. The DSMB will hold scheduled meetings prior to commencement of data

collection, at 3 months after data collection has started and at the end of the study. These meetings will be headed by the clinical pharmacologist who will be the chairperson of the DSMB.

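### Section 2.9.5.1 lets the code be broken before study completion only on a DSMB recommendation, with no exception for a medical emergency in one participant and no timed route to such a recommendation

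*Protocol*

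**What the plan says.** Section 2.9.5.1 gives one rule for the period before study completion: "Breaking the code will only occur upon recommendation by the Data and safety monitoring board (DSMB) during the study duration". The next section covers the period afterwards: "The study drug codes will only be available once all data collected will have been entered into the database for every participant".

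Custody of the code follows the same line. Under section 2.9.3 the sealed allocation envelopes "will remain with the statistician who will give it to the investigator at the time of data analysis". Section 2.9.4 says that "all members of the research team and the subjects will be blinded to treatment allocation". It names two exceptions: the statistician who prepares the schedule, and the independent pharmacist "who will label the study drug boxes with the arbitrary study letters will be unblinded".

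On the DSMB, section 2.15.2 schedules meetings before data "collection, at 3 months after data collection has started and at the end of the study". The same section makes staff responsible for coordinating the response to SAEs and "reporting these if indicated to the investigator, who will then report to the appropriate board/committee".

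**The concern.** A blinded drug trial normally lets one participant's allocation be disclosed quickly when that person's care depends on it, and keeps disclosure of whole arms for an independent board. Section 2.9.5.1 puts both decisions with the board. Because it says *only*, it is a stated restriction and not a detail left for another document to supply.

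The study drug makes the question relevant. Section 1.1 describes low-dose aspirin as an antiplatelet and names gastrointestinal and, rarely, cerebral bleeding among its risks, although it reports these as not life-threatening and likelier at high doses. If a clinician needs to know whether a participant has been taking 75 mg of aspirin, the site must either manage without the answer or depart from the protocol and improvise a disclosure. The first is a safety weakness. The second puts the blind at risk in an uncontrolled way.

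**Working it through.** No power, sample size or error rate enters this point. The check sets side by side every section that could provide an emergency exception or a rapid route to the board.

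| Section | What it provides | Exception for one participant? | Timed route to the DSMB? |
|---|---|---|---|
| 2.9.5.1 | Code break before completion only on DSMB recommendation | No | No |
| 2.9.5.2 | Codes released after the database is finalised | No | No |
| 2.9.3 | Envelopes stay with the outside statistician until analysis; no site copy described | No | No |
| 2.9.4 | Research team and participants blinded; statistician and independent pharmacist unblinded | No | No |
| 2.12.4.1 | SAEs reported to two ethics committees within 24-72 hours | No | DSMB not named |
| 2.12.4.2 | SUSARs reported within 15 days, or 7 days if fatal or life-threatening | No | DSMB not named |
| 2.15.1 | On bleeding, stop study drug, assess at once, manage | No | No |
| 2.15.2 | Three scheduled DSMB meetings; SAEs passed on to an unnamed board or committee | No | No time limit, contact or procedure |

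From this:

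1. The rule is closed. Nothing in 2.9.5.1 or elsewhere lets a clinician's request lead to disclosure.
2. The one permitted route has no written procedure. Section 2.15.2 can be read to include the DSMB among the bodies told of an SAE, but it does not connect that report to a code break or say how fast either should happen.
3. The people needed for a remedy already exist. Section 2.9.4 leaves two people unblinded, and the statistician is outside the study under 2.9.3.
4. Care can often proceed without the code. Study drug is stopped on bleeding (2.15.1). A participant who must take an antiplatelet or anticoagulant is withdrawn (2.8.4, 2.9.6.1). Appendix 5 permits prophylactic low molecular weight heparin for inpatients with the blind intact. A clinician can also act as though the participant took aspirin. With 1:1 allocation that presumption is wrong for about half of participants, but it is the cautious choice when bleeding is the worry.
5. Disclosure needs care. All boxes carry one of two letters, P or Q (2.8.1.1, 2.9.3), and participants return their boxes to the study doctor for tablet counts (2.8.3). Someone who learns one participant's arm and letter can decode others whose letter is known.

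**The case against.** The strongest reply is that no concrete need is shown. Bleeding, the named hazard, already triggers stopping and assessment. Section 2.9.2.2 excludes people with aspirin intolerance, asthma, a bleeding tendency, antithrombotic therapy, peptic ulcer disease or severe renal disease. The comparison is 75 mg daily with placebo for six months. This largely stands, and it is why the consequence is rated modest. It does not supply the missing provision: stopping a drug does not tell a clinician whether an antiplatelet was taken.

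A second reply is that the restriction has a purpose. With two letters, breaking one code may break many, so an independent board protects the blind. That is a fair reason to control disclosure carefully and it shapes the fix. It is not a reason to have no emergency route.

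A third is that the DSMB could be consulted out of session. Nothing bars this, but nothing says how or how fast.

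Two stronger readings are tempting, and the protocol does not support them.

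- From the meeting schedule and section 2.5 ("The proposed study is expected to run for 1 year, from start of subject screening to last subject finishing the study") a reader might infer that a clinician could wait about 12 - 3 = 9 months, or that the share of treatment time after the month-3 meeting measures the problem. Section 2.9.5.1 requires a recommendation, not a scheduled meeting. An emergency lasts hours, so even monthly meetings would not serve it.
- A reader might infer that the present rule exposes up to 227 allocations at a site, or all 454 if the letters mean the same at both sites. Those are ceilings on what a disclosure under two-letter coding could reveal. The current text restricts disclosure, so they are a risk of an improvised or badly designed code break and not a result of the rule.

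**Conclusion.** The point holds as a cheap safety improvement. The protocol fixes a DSMB recommendation as the sole route to a code break before completion, gives no exception for one participant's emergency, and describes no timed way to get the recommendation. The clinical consequence is modest, because the stopping and withdrawal rules and the option of presuming aspirin exposure cover much of what a clinician would need. The protocol gives no rate of emergencies in which the allocation would alter care, so none is estimated. The conclusion assumes that no separate unblinding procedure outside this protocol overrides 2.9.5.1; the protocol refers to none. The design, the sample size and the analysis are not affected.

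**What to change.** Amend 2.9.5.1, with short cross-references in 2.9.3 and 2.9.5.2, to provide that:

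- one participant's allocation may be disclosed at once, at the treating clinician's request, when it is needed for that participant's care;
- the statistician makes the disclosure, with the independent pharmacist as back-up, both being already unblinded under 2.9.4;
- the date, the reason and the persons informed are logged, and the DSMB is notified afterwards;
- the participant stays in the intention-to-treat analysis (2.13.2) and in follow-up, as 2.9.6.1 already provides for withdrawals;
- unblinding of whole arms remains with the DSMB.

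Because of the P/Q coding, disclose only to the clinician giving the emergency care, outside the trial team where possible. Disclosure outside the team is not enough by itself: section 2.15.2 sends drug-related SAEs to the study clinician, and lettered boxes come back to the study doctor. The amendment should therefore say who receives the code in that case, and should have the participant's remaining boxes returned to the independent pharmacist instead of the study doctor.

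Labelling boxes by study number in place of P/Q, and removing the letters from the site schedule, is the fuller safeguard, since one disclosure would then reveal one allocation. It is optional. It means amending 2.8.1.1 and 2.9.3 and writing study numbers on about 454 x 6 = 2,724 boxes, assuming one box per participant per month, after which boxes cannot be swapped between participants.

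The cost of the main change is a few sentences, a contact reachable at all times (the budget in section 3.1 has no line for one), and a few unblinded participants to flag in the report.
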